## Methods

### Study design

The study uses a two-arm cluster site-randomized design. Additionally, a pre-post intervention two-sample design is nested within the intervention arm to assess the incremental effectiveness of CIS + FI compared to CIS without FI on study outcomes. One cohort of participants (cohort 1) is enrolled in the SOC arm and two cohorts (cohorts 2 and 3) are enrolled sequentially in the intervention arm (Figure 2). Cohort 2 receives CIS consisting of POC CD4 count testing at time of HIV testing, accelerated ART initiation, and cellular appointment reminders and is enrolled concurrently to cohort 1 in the SOC arm; outcomes among cohort 2 will be compared to those among cohort 1. Cohort 3 receives CIS + FI, consisting of CIS plus FI at key points in the HIV care continuum and is enrolled following enrollment of all participants in cohort 2 in the CIS arm; outcomes among cohort 3 will be compared to those among cohort 2.

**Figure 2 Fig2:**
[figure not shown]
**Overview of study design.**

### Study sites and participants

The study site is defined as a primary health facility providing both HIV testing and HIV care and treatment services. Within a given health facility, all HIV testing and counseling (HCT) points are included with the exception of prevention of mother-to-child transmission (PMTCT) and Tuberculosis (TB) clinic points of testing, as these testing points follow different linkage to care procedures. Primary health facilities were chosen as study sites, rather than larger provincial hospitals, as they reflect the decentralized HIV care system in Mozambique in which HIV services are provided in an outpatient clinic setting. A total of 10 sites were selected from the 66 health facilities in the region based on existing data suggesting they had sufficient numbers of patients testing HIV positive and enrolling in HIV care to meet the study sample size needs (see below) (Table 1). Sites are randomized to the SOC arm or the intervention arm using matched-pair randomization with matching done by facility location (rural, peri-urban, or urban) and expected number of adults enrolling in HIV care at each facility per month.

**Table 1 Tab1:** **Study sites, randomization assignments, and HIV counseling and testing points**

Matched pair	Province	Facility	Randomization assignment	Urban/Rural locale	HIV testing point for study enrollment	Number of enrollees in HIV care
**1**	Maputo City	Bagamoio	CIS	Urban	VCT	>170 per month
	Maputo City	Mavalane	SOC	Urban	PICT*	>170 per month
**2**	Inhambane	Urbano	CIS	Urban	VCT	< 170 per month
	Inhambane	Maxixe	SOC	Urban	VCT	< 170 per month
**3**	Maputo City	Jose Macamo	SOC	Peri-urban	VCT	>170 per month
	Maputo City	Zimpeto	CIS	Peri-urban	VCT	>170 per month
**4**	Inhambane	Massinga	SOC	Peri-urban	VCT	< 170 per month
	Inhambane	Chicuque	CIS	Peri-urban	VCT	< 170 per month
**5**	Inhambane	Morrumbene	SOC	Rural	PICT**	< 170 per month
	Inhambane	Zavala	CIS	Rural	VCT	< 170 per month

*Mavalane = Psychosocial services testing point; **Morrumbene = Triage testing point.

The target study population includes 2,250 treatment-naïve adults who newly test HIV positive at study sites: 750 in the SOC arm (cohort 1), 750 in the CIS cohort of the intervention arm (cohort 2) and 750 in the CIS + FI cohort of the intervention arm (cohort 3), with an average of 150 participants per site. Study participants must be 18 years of age or older, test positive at the participating HCT point within the health facility with written proof of test result, agree to be referred to HIV care services within the health facility, agree to provide contact information, agree to adhere to study procedures and be able to provide informed consent. Study participants without access to cellular phones and those who are illiterate are included. Those without access to cellular phones enrolled at intervention sites are unable to receive the SMS component of the intervention; this information is tracked by the study staff. Exclusion criteria include being pregnant at the time of study enrollment, planning to leave the community in the next 12 months, having enrolled in HIV care in the past six months at any health facility, having initiated ART (for any duration) in the past six months at any health facility, currently taking ART, or being unable to speak or understand Portuguese or Xitsua.

Participants are recruited and enrolled immediately following HIV diagnosis at the sites. After patients receive a positive HIV test result, post-test counseling, and in the case of intervention sites, POC CD4 count testing and pre-ART counseling if eligible for ART, clinic staff informs them about the study and directs those interested in participating to study staff for more information. Study staff further explains the study and if the patient is interested, screens them for eligibility and completes the informed consent process.

### Study interventions

#### Standard of Care (SOC)

At sites randomized to the SOC arm, patients are managed per current Mozambican Ministry of Health (MOH) guidelines (Table 2). HCT counselors refer patients diagnosed with HIV to attend HIV care services at their preferred health facility as soon as possible. In most cases, patients are verbally referred to the on-site HIV care and treatment clinic. Patients who present to the health facility receptionist to enroll in HIV care are scheduled for an appointment for clinical consultation in the on-site HIV clinic. Following the clinical consultation, patients are sent to the health facility laboratory to have blood drawn for CD4 count testing and baseline laboratory tests. Laboratory tests are processed at the health facility laboratory in four of the five SOC sites, and are sent off-site for processing at the remaining SOC site. Patients are asked to return for another clinical consultation approximately one to two weeks later to review laboratory results, at which point ART eligibility is determined by CD4 count and WHO stage following national guidelines: CD4 count ≤350 cells/μL and/or WHO stage III/IV. Those who are ART eligible receive on average three counseling sessions before initiating treatment. Patients receiving ART are requested to return to the health facility every two weeks for the first month, at two months, at six months, and then every six months thereafter. Patients not eligible for ART are requested to return in six months for clinical evaluation and routine laboratory testing. Peer educators follow-up with patients who miss appointments on ad hoc basis via phone or home visits.

**Table 2 Tab2:** **Combination intervention strategy interventions compared to standard of care**

Intervention	Standard of care	CIS (CIS, CIS + FI)	Barriers targeted by interventions
**CD4 testing**	CD4 (Cyflow, FACS Caliber/Count, POC CD4) at HIV care site laboratory if linkage completed.	POC CD4 assays at HIV testing points.	Structural
	Turnaround time: 1–4 weeks.	Turnaround time: immediate.	
**Accelerated ART initiation**	Within 1–2 months from linkage.	Accelerated ART initiation within 1 week from testing.	Biomedical
	2-3 counseling sessions, all in HIV care.	2 counseling sessions, one in HCT immediately following POC CD4 test and one in HIV care.	
	Baseline laboratory tests results obtained prior to initiation.	Draw blood for baseline laboratory tests, and initiate prior to results.	
**Cellular appointment reminders**	None.	SMS appointment reminders for all participants.	Behavioral
**Non-cash financial incentives**	None.	Pre-paid cellular air time cards.	Structural

#### Combination Intervention Strategy (CIS)

In order to most closely approximate “real-life” service delivery, the clinical interventions of the CIS package (i.e. POC CD4 count testing and accelerated ART initiation) are provided by clinic staff to all patients receiving care at the facility, not solely study participants. Study personnel provide SMS appointment reminders and, for participants in the CIS + FI cohort, FI only to study participants. Each of these interventions is described below.

#### POC CD4 count testing

Patients at the intervention sites receive a POC CD4 count test in the HCT point of service immediately following HIV diagnosis by the HCT counselor. Results are available and provided to the patient along with an explanation of their meaning within 20 minutes. All patients, regardless of CD4 count, are provided with a referral slip for the on-site HIV care clinic and instructed to enroll in care as soon as possible, although particular emphasis on prompt enrollment is provided to patients who are ART eligible as described below. Patients not yet eligible for ART who agree to enroll in HIV care immediately are escorted to the receptionist’s office, whereas those who are ART eligible receive the accelerated ART initiation intervention described below.

#### Accelerated ART initiation for eligible patients

Patients with CD4 count ≤350 cells/μL as measured by POC CD4 count testing receive referral for accelerated ART initiation. Immediately following the POC CD4 count measurement, the HCT counselor provides the first pre-ART counseling session, in contra-distinction to the SOC arm where it is provided only after the patient links to care and receives a clinical consultation. Following the counseling session, the counselor escorts the patient to the receptionist’s office for immediate enrollment in HIV care and prompt ART initiation. The receptionist expedites scheduling of ART-eligible patients for a clinical consultation so that it is scheduled as soon as possible, ideally on the same day. Patients proceed immediately to have baseline laboratory tests drawn. At the clinical consultation, the clinician evaluates the patient for ART initiation, and refers the patient for additional pre-ART counseling if necessary. Medically eligible patients are initiated on ART on the same day as their clinical consultation and prior to receipt of laboratory results.

#### Cellular appointment reminders

During the first month following study enrollment, study participants receive weekly reminders via text messages to link to care (“*Hi. Your health is the most important thing. Please remember to come to the health center for health services*”). For the remaining 11 months of their enrollment in the study, participants receive monthly reminder messages to remain engaged in care (“*Hi. Continue coming to the health center to take care of your and your family’s health*”). In addition, participants who successfully link to HIV care receive appointment reminders tailored to their upcoming appointments (“*Hi. Your health is the most important thing. We expect to see you at your upcoming appointment scheduled for the day X*”). In order to maintain participant confidentiality, cellular appointment reminders do not refer to HIV, HIV care services, a specific health facility, or reveal any personal information. Participants are not asked to confirm receipt or reply to any messages.

#### Non-cash financial incentives

Participants in the CIS + FI cohort receive CIS interventions plus a series of non-cash FI in the form of pre-paid cellular air time cards. The non-cash FI air-time cards are valued at approximately $5 USD and are provided upon the following achievements: linkage into care within 1 month of testing, and engagement in care by visiting the health facility for HIV care and treatment services at six months and 12 months following study enrollment, for a total of $15 USD over the study period.

### Data collection

Data collection consists of participant interviews, extraction of patient-level data from medical records, and site assessments.

#### Participant interviews

Participant interviews are conducted at baseline, and one month and 12 months after study enrollment by study staff using closed-ended questionnaires. The baseline questionnaire collects information on patient socio-demographics, travel to and time spent at the HIV clinic, and HIV testing history. The 1-month and 12-month questionnaires collect information on linkage to care and retention in care. All three questionnaires collect information on quality of life and social support, perceived and experienced HIV stigma, and HIV knowledge and beliefs. Additionally, for patients in the intervention arm, the follow-up interviews assess patient receipt and acceptability of each intervention component. Baseline interviews are completed at the health facility following receipt of informed consent and contact information for follow-up interviews. For the 1-month and 12-month follow-up interviews, study staff makes up to four attempts to reach the participant by phone to complete the interview. If the participant cannot be reached by phone, study staff conducts home visits in an attempt to locate the participant and conduct the interviews. Additionally, participants who are reached by phone and indicate a preference to return to the health facility to complete the interview may do so.

#### Extraction of patient-level data from medical records

Upon study completion, clinical and immunological data required to construct the primary study outcomes of linkage and retention and other variables of interest are extracted from existing electronic patient-level databases. Data are also used to assess comparability of the study population to the entire HIV care clinic population enrolled during the study period.

#### Site assessments

Data on the configuration of HIV services at the ten study sites are collected at the beginning and at the end of the study using a standardized site assessment form.

#### Cost data

Costs of delivering the SOC, CIS and CIS + FI are estimated by measuring utilization rates and multiplying utilization by the resource expenditure per unit utilization: laboratories, outpatient visits, inpatient visits, patient time and transportation costs, staff time, expenses for staff training, durable equipment and non-durable equipment used by staff, and rent.

### Sample size and power analysis

Based on a review of the relevant literature, under the current SOC in Mozambique we conservatively estimated that the combined outcome of linkage within 1 month and retention at 12 months after HIV diagnosis would be 25% (assuming 50% of participants enroll into HIV care within 1 month of diagnosis and 50% of these are retained in care 12 months after diagnosis). We then estimated the minimum difference we could detect in our combined outcome between CIS and SOC arms with 80% power using the Power and Sample Size (Pass 8.0) software for two independent proportions in a cluster randomization study design and a two-sided Farrington & Manning Likelihood Score Test [34], and assuming five study clusters (two sites per cluster) and 300 patients per cluster. With these assumptions, we will have 80% power to detect as statistically significant a relative risk of the combined outcome of linkage and retention between CIS and SOC arms of 1.6 (or an absolute increase in the combined outcome of 20%) comparing the CIS to SOC arms.

To address the objective of comparing the effectiveness of CIS + FI to CIS on the combined outcome of linkage within 1 month of diagnosis and 12 month retention after diagnosis, we are enrolling an additional 150 participants in each of the five CIS sites (total of 750 additional participants in intervention arm) in cohort 3 (CIS + FI) upon completion of enrollment of cohort 2 (CIS). Assuming that the combined outcome of linkage within one month of diagnosis and retention 12 months after diagnosis is 45% in the CIS arm, we will also have greater than 80% power to detect an absolute increase of 21% in the combined outcome comparing CIS + FI to CIS.

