**Methods/Design:**

We are conducting an implementation science study using a two-arm cluster site-randomized design to determine the effectiveness of a combination intervention strategy (CIS) using feasible, evidence-based, and practical interventions—including (1) point-of-care (POC) CD4 count testing, (2) accelerated antiretroviral therapy initiation for eligible individuals, and (3) SMS reminders for linkage to and retention in care—as compared to the standard of care (SOC) in Mozambique in improving linkage and retention among adults following HIV diagnosis. A pre-post intervention two-sample design is nested within the CIS arm to assess the incremental effectiveness of the CIS plus financial incentives (CIS + FI) compared to the CIS without FI on study outcomes. Randomization is done at the level of the study site, defined as a primary health facility. Five sites are included from the City of Maputo and five from Inhambane Province. Target enrollment is a total of 2,250 adults: 750 in the SOC arm, 750 in the CIS cohort of the intervention arm and 750 in the CIS + FI cohort of the intervention arm (average of 150 participants per site). Participants are followed for 12 months from time of HIV testing to ascertain a combined endpoint of linkage to care within 1 month after testing and retention in care 12 months from HIV test. Cost-effectiveness analyses of CIS compared to SOC and CIS + FI compared to CIS will also be conducted.

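### The detectable effect for CIS versus SOC contradicts itself: from 25%, a relative risk of 1.6 is +15 points, not +20, and matched pairs are described as clusters

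*Protocol article*

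**What the plan says.** All the planning figures are in the section Sample size and power analysis of the protocol article.

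- **SOC rate.** The combined outcome of linkage and "retention at 12 months after HIV diagnosis would be 25" percent, built as 50% linking times 50% of those retained.
- **Claim for CIS versus SOC.** The text says "we will have 80% power to detect as statistically significant a relative risk of the combined outcome", and gives its size as a ratio "between CIS and SOC arms of 1.6 (or an absolute increase in the combined outcome of 20" percent.
- **CIS rate used for the next comparison.** The following paragraph takes it that "retention 12 months after diagnosis is 45% in the CIS arm", and claims "greater than 80% power to detect an absolute increase of 21% in the combined outcome" for CIS + FI over CIS.
- **Clusters.** The calculation was done "assuming five study clusters (two sites per cluster) and 300 patients per cluster", using a two-sided score test for two independent proportions in a cluster randomised design.

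Other sections describe the layout differently. The abstract states: "Randomization is done at the level of the study site, defined as a primary health facility". Study sites and participants, with Table 1, lists ten sites in five matched pairs, one site of each pair in each arm, with 750 participants in the SOC arm, 750 in the CIS cohort and an average of 150 per site. Statistical methods puts the random effects on sites.

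**The concern.** The ratio and the difference stand in one sentence as equivalent descriptions of one effect. They are not equivalent at the stated SOC rate, so the reader cannot tell which effect the 80% refers to. This is the planning figure for the primary comparison, and it will be used to interpret the result. A reader who takes 1.6 as the detectable effect will believe that the trial could reliably find a rise from 25% to 40%. A reader who takes +20 points will expect that only for a rise to 45%. A non-significant result means different things under the two readings.

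The cluster wording adds a second obstacle. A matched pair has one site in each arm, so it is not a unit allocated to an arm. It cannot serve as the cluster in a comparison of two independent groups of clusters, and the stated calculation cannot be repeated from its own description.

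**Working it through.** **Inputs.** SOC rate 25%; stated effects 1.6 and +20 points; CIS rate carried forward 45%; five sites per arm at 150, so 750 per arm (all from the article). The article gives neither the significance level nor the ICC. I assume two-sided 5% and show a range of ICCs.

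**1. The two effects.**
- 0.25 × 1.6 = 0.40, a difference of 15 points.
- 0.25 + 0.20 = 0.45, and 0.45 / 0.25 = 1.8.
- Both statements hold only if 0.6 × p = 0.20, that is p = 33.3%, a rate that appears nowhere in the article.

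**2. The ICC at which each effect has 80% power.** With unpooled variance, the design effect that leaves 80% power is

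DEFF = 750 × d² / [(1.960 + 0.8416)² × (p1q1 + p2q2)], and ICC = (DEFF − 1) / 149.

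- +20 points: 750 × 0.04 / (7.849 × 0.4350) = 8.79, so ICC = 7.79 / 149 = 0.052.
- +15 points: 750 × 0.0225 / (7.849 × 0.4275) = 5.03, so ICC = 4.03 / 149 = 0.027.

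With pooled variance under the null, the values are 0.050 and 0.026. The two effects tolerate ICCs that differ about twofold. At the ICC where +20 points has exactly 80% power, a ratio of 1.6 has 57% (pooled; 56% unpooled).

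**3. Can the stated 80% be reproduced?** Not strictly, because no ICC is given. It is plausible for +20 points. At an assumed ICC of 0.05, DEFF = 1 + 149 × 0.05 = 8.45:
- 25% versus 45%: SE = √(0.4350 × 8.45 / 750) = 0.0700; 0.20 / 0.0700 = 2.86; power 81.5% (80.3% pooled).
- 45% versus 66%, treated as independent groups: SE = √(0.4719 × 8.45 / 750) = 0.0729; 0.21 / 0.0729 = 2.88; power 82%.
- 25% versus 40%: SE = √(0.4275 × 8.45 / 750) = 0.0694; 0.15 / 0.0694 = 2.16; power 58% (57% pooled).

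One ICC of about 0.05 therefore fits both the 20-point and the 21-point claims, but not 1.6.

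**4. Range of ICC, five sites of 150 per arm** (unpooled variance; the t columns use a non-central t on 10 − 2 = 8 df):

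| ICC | RR 1.6, normal | RR 1.6, t | +20 points, normal | +20 points, t |
|---|---|---|---|---|
| 0.01 | 98% | 94% | >99% | >99% |
| 0.02 | 88% | 79% | 99% | 95% |
| 0.03 | 77% | 65% | 94% | 87% |
| 0.05 | 58% | 48% | 81% | 71% |
| 0.10 | 35% | 28% | 55% | 45% |

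**5. The cluster description.** Five pairs × 2 sites × 150 = 1,500 = 750 + 750, so the total is right and the five units of 300 are the five matched pairs. If five clusters of 300 per arm had been entered instead of five of 150, power would change little: at ICC 0.05 for +20 points, 84% against 81%; at ICC 0.03 for +15 points, 80% against 77%.

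**The case against.** The strongest reply is that this is a slip in one number. The 45% carried forward and the fit of a single ICC to both the 20- and 21-point claims suggest that 1.6 was written where 1.8 was meant. The article is also a condensed account that points to a full protocol, so a missing ICC is no fault in itself. The correction changes no sample size, endpoint or analysis, and by July 2014 eight of the ten sites had completed enrolment. All of this stands, and it limits the point to a wrong statement rather than a failed design. It does not remove the contradiction, which needs no assumption and sits in the headline planning figure.

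Stronger conclusions are tempting, and the article does not support them:

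- *The 80% power claim is wrong.* Without an ICC it can be neither reproduced nor refuted, and for +20 points it is plausible by normal approximation.
- *The trial lacks the clusters it planned on, or needed 1,500 per arm.* The article never says five clusters of 300 in each arm; the units are the matched pairs, and the total agrees.
- *A true ratio of 1.6 would more likely than not be missed.* At ICC 0.05 the normal calculation gives 58%. It falls below half (48%) only if a t reference is added to that assumed ICC, and at ICC 0.02 power is 79% even on 8 df.

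**Conclusion.** The sentence is wrong as written. At the stated 25% SOC rate, a relative risk of 1.6 and an increase of 20 points are 40% and 45%, and a single 80% power statement cannot be the minimum detectable effect for both. The gap matters: where +20 points just reaches 80%, a ratio of 1.6 has about 57% (normal approximation, five sites of 150 per arm, two-sided 5% assumed). The 45% used for the second comparison favours +20 points as the intended effect, but only the original calculation can settle that.

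The cluster description is also wrong, because it names the matched pair where the site is the randomised unit. Its numerical effect is probably small.

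With only ten sites, a large-sample test is somewhat optimistic for planning. How much depends on the ICC, so the 8 df figures above are illustrations and not a corrected power for this trial.

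**What to change.** 1. Go back to the original software output and confirm which effect it returned. State that effect once, with ratio and difference in agreement: 25% versus 45%, relative risk 1.8, +20 points, if 45% was intended.
2. Replace the description of five two-site clusters of 300 by five sites per arm of about 150 participants each.
3. Restate the power for that layout with the ICC and significance level actually used, preferably with a t reference because there are only ten sites. For illustration, +20 points has about 81% power by normal approximation and 71% on 8 df at an assumed ICC of 0.05, and 94% and 87% at 0.03. The assumed values should not be copied into the protocol in place of the real one.

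The cost is a text correction and possibly a less favourable stated figure. No additional participants are needed, and the design and the planned analysis stay as they are.
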